### 7.1.2. Secondary study parameters/endpoints

Secondary parameters/endpoints:

- The absence of any effect.
- Safety, assessed by tolerance and adverse event profiles.
- Acceptance of study medication by subjects, indicated on a 5-point rating scale:

0= not acceptable

1= somewhat acceptable

2= moderately acceptable

3= acceptable

4= very acceptable

Patient satisfaction is assessed on the basis of 3 statements. Here patients can express to what extent they agree with the statement. For the extent of agreement a 5-point rating scale is used ranging from total disagreement (-2) to total agreement (+2).

See also trial monitor forms: Annex F4

### 7.1.3. Other study parameters

Other study parameters (baseline characteristics) will be presented in a table.

These other parameters are age, sex, count and average size of FF, previous treatment for FF, age of presentation of FF, other medication used during the trial, medical history.

## 7.2 Randomisation, blinding and treatment allocation

Sides to be treated will be randomized according to a computer randomisation program in blocks of 4. An independent statistician will prepare the randomisation list. Rapamycin and placebo will be packaged in identical bottles with a code number according to the randomisation list. Because of participation of two centres, stratification will take place by allocating entire blocks to a centre. The list of randomisation will be kept at a secure place away from the investigator.

Medication is prepared by Wyeth pharmaceuticals and delivered to the pharmacy of VU Medical Centre Amsterdam. There medication will be labelled with study number and facial side to be treated where LEFT and RIGHT are taken to be determined from the patient’s POV. Patient and physician are blinded until the end of the study.

If at any visit a clear difference arises between treated sides the binding will be broken. If better side is the rapamycin treated one, we will continue with an open-label study. If the better side is the placebo-treated side or the study shows that topical rapamycin has no effect at all, the trial will be terminated prematurely.

Besides unblinding in the situation described above, the code may be broken for a particular subject in case of a suspected serious adverse event. In all other situations unblinding will take place after allocating participants to the relevant analyses populations, just before the primary statistical analysis.

## 7.3 Study procedures

Conduct of the study

The first visit (screening) includes:
- In- or exclusion, in case of inclusion:

- Physical examination according to protocol, especially lesion size and count
- Biopsy of a representative tumour (if not yet undergone one)

- The patient already has the patient information; this has been sent before the first visit.

- For women: pregnancy test

The second visit (baseline) includes:

- Physical examination according to protocol

- Standardized medical photography of the face. (All photos will be assessed by the investigator and two independent physicians).
- Instruction of patient (see Annex E4), provide study medication according to randomization

Follow-up visits will take place at 3 months and at 6 months. At each follow-up visit, unused study medication will be taken back and new medication is dispensed. Unused medication is weighed to ensure protocol compliance.

At the first follow-up visit at 3 months it will be assessed if unblinding is needed.

Physical examination and medical photography are part of regular care/medical treatment.

Treatment with rapamycin solution (and placebo solution) and pregnancy tests are part of the study.

See also trial flow-chart: Annex F4.

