## 6.7 Preparation and labelling of Investigational Medicinal Product

Prior to start of the study, rapamycin oral solution will be provided by Wyeth pharmaceuticals. ACE Pharmaceuticals in Zeewolde will be responsible for packaging and labelling the study medication. They will also produce the placebo solution. Rapamune and placebo solution will be packaged in amber glass 20 ml bottles. Decanting of rapamune will take place at a temperature of 2-8 °C at nitrogen conditions to preserve solution quality.

As described above the study medication will be delivered in 20 ml bottles, 6 for each facial half, fitted with a syringe adapter. With a dosing syringe patients withdraw 0,25 ml solution twice daily. . Coding of bottles will be according to the randomisation list.

The following information shall appear on the labels:

ALLEEN VOOR GEBRUIK BIJ KLINISCHE STUDIE

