**RECHTS** of **LINKS**

Vloeistof, voor uitwendig gebruik.

2x daags aanbrengen op het gezicht.

Zie patiënten informatie voor meer gegevens.

Studienummer: xxxxx

Houdbaarheid na openen: 1 maand

Bewaren in de koelkast (2-8˚C)

Buiten het bereik en zicht van kinderen bewaren.

Because of a 30 day shelf life of an opened bottle, decanting of rapamune - that requires opening bottles – will be done in 6 stages, ones every month. After preparation at ACE Pharmaceuticals the study medication will be sent directly to the patient by post, so treatment can start immediately. In this way we can guarantee a good quality of rapamune, as patients will be out of solution in exactly one month.

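### Sections 6.6, 6.7, 7.2 and 7.3 give incompatible instructions on labelling and supply, and neither the bottle label nor the stated volumes enforce the protocol's own 30-day limit

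*Protocol*

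**What the plan says.** **Packaging and labelling.** Section 6.7: "ACE Pharmaceuticals in Zeewolde will be responsible for packaging and labelling the study medication". Section 7.2: "Medication is prepared by Wyeth pharmaceuticals and delivered to the pharmacy of VU Medical Centre Amsterdam", and it is at that pharmacy that study number and facial side are put on the label. Section 6.6 lists label items, including visit number and distribution date, that do not appear on the label text printed in 6.7.

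**Delivery.** Section 6.7 gives a reason for staged preparation: "Because of a 30 day shelf life of an opened bottle", and decanting is a step "that requires opening bottles", so it "will be done in 6 stages, ones every month". It continues: "After preparation at ACE Pharmaceuticals the study medication will be sent directly to the patient by post, so treatment can start immediately". It adds that product quality is thereby guaranteed, since the patient's supply ends after one month. Section 7.3 instead provides medication at the baseline visit and states: "At each follow-up visit, unused study medication will be taken back and new medication is dispensed". Follow-up visits are at months 3 and 6.

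**Label.** The printed text reads "Houdbaarheid na openen: 1 maand" (shelf life after opening: one month). It carries no decanting date and no use-by date.

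**Volumes and duration.** Section 6.7: 20 ml bottles, six per facial half, 0.25 ml withdrawn twice daily. Section 5.1: treatment for 6 months. Section 7.3: returned medication is weighed as a compliance check.

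**The concern.** The 30-day limit is the protocol's own condition for the quality of the active product. It can be kept only if everyone knows who prepares each bottle, when it reaches the patient and when it expires. The sections disagree on the first two. On the third, the label starts the clock at a different event from the one 6.7 reasons from.

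The statistical interest lies in the split-face design. Placebo contains no drug to lose, so any loss of strength through late use would act on one side of each pair only and push the within-patient comparison toward no difference. The side marked on the bottle is also the treatment allocation, so responsibility for that label should be unambiguous. Finally, weighing returns measures compliance only if the starting volume is known.

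**Working it through.** **1. The plan's own figure: run-out in exactly one month (6.7).**
Inputs: 20 ml per bottle; 2 × 0.25 ml = 0.5 ml/day, read as the amount for each facial half (6.7 does not say so explicitly).
- Days per bottle = 20 / 0.5 = 40 days.
- Volume for 30 days = 30 × 0.5 = 15 ml, leaving 20 − 15 = 5 ml, or 10 further days.

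The figure is not reproduced from the nominal volume. It would hold with a fill of about 15 ml, but no fill volume is stated. The bottle count does fit monthly supply: 6 bottles × 30 days = 180 days.

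**2. When the 30 days start.** Section 6.7 gives the shelf life of an opened bottle as the reason for decanting monthly, because decanting opens the stock bottle. That argument works only if the clock starts at decanting. The label's clock starts at opening, which a patient may well take to mean opening the study bottle. Time between decanting and first use is then not counted.

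**3. Monthly posting (6.7).** Share of doses beyond 30 days, for 30 days' use starting *lag* days after decanting = lag / 30.
- Lag 0: 0%.
- Lag 3 days (an assumed value): 3/30 = 10%.
- If a full 20 ml bottle were used to the end with no lag: 10/40 = 25% of that bottle's doses.

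**4. Visit dispensing as the only route (7.3), worst case.** Assumptions: posting does not occur, each 3-month supply is decanted in one session, and twice-daily use is maintained. Share beyond 30 days = (interval + lag − 30) / interval.
- 90 days, lag 0: 60/90 = 67%.
- 91 days, lag 0: 61/91 = 67%. Over two intervals this is 61 × 2 × 2 = 244 of 364 applications to the active side.
- 91 days, lag 7: 68/91 = 75%.
- If instead one full 20 ml bottle per side were given at each visit, it would cover 40 of 91 days (44%), with 10/40 = 25% of its doses late.

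**5. Weighing of returns (7.3).** Suppose a bottle comes back after 30 days with 5 ml left. With a 20 ml fill, 15 of 15 ml were used, which is full compliance. With a 15 ml fill, 10 of 15 ml were used, or 67%. Without the fill volume the two cannot be told apart.

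**6. Month 6.** Six months of treatment (5.1) and six bottles per half (6.7) are complete at month 6, yet 7.3 dispenses at every follow-up visit without saying to whom.

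**The case against.** The strongest reply is that the alarming figure needs a scenario the protocol never states. Section 7.3 gives no quantity, does not say that several months' bottles are decanted together, and does not rule out posting between visits. The only text on decanting, in 6.7, sets six monthly stages precisely to respect the limit. A reader might infer that the plan puts most active doses beyond 30 days; the documents do not support that. This objection stands, so 67% is a worst-case illustration only. It does not remove the conflict, because no section says that visit dispensing supplements posting, and direct posting so that treatment can begin sits badly with first provision at the baseline visit.

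Three further replies also stand in part.
- **Bias.** A reader might infer that the comparison is biased. No degradation rate is given, and 6.7 describes decanting cold and under nitrogen to protect quality. Only the direction of a possible effect can be stated.
- **Allocation.** Two labelling sites might suggest swapped sides. Sections 6.7 and 7.2 both tie bottles to the randomisation list, which 7.2 has prepared by an independent statistician. The responsibility is duplicated; a mechanism for misallocation is not shown.
- **Month 6.** Dispensing then could serve patients in the open-label continuation described in sections 3 and 7.2. It is unqualified rather than plainly wrong.

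The patient instruction (Annex E4) and flow chart (Annex F4) are not at hand and may clarify how bottles are to be used. They would not remove the conflict within the protocol text.

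**Conclusion.** The inconsistency is real and should be corrected. Sections 6.6, 6.7, 7.2 and 7.3 cannot all be followed on who labels the medication and how it reaches the patient. Separately, even under the monthly posting route, the 30-day limit is not secured: the label starts its clock at opening, and the run-out safeguard fails on nominal volumes by 10 days (40 against 30), unless the fill is about 15 ml.

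How much late use would result depends on the route actually used. Under posting it is confined to transit, waiting time and any leftover solution. Only with visits as the sole route and joint decanting does it reach about two thirds of active doses (67% to 75% for lags of 0 to 7 days). These figures assume 0.5 ml/day per facial half. The effect on the treatment comparison cannot be computed from the documents, so this is a matter of product control and documentation and does not demonstrate a flaw in the efficacy analysis.

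**What to change.** - Reconcile 6.6, 6.7, 7.2 and 7.3 to one supply route and one labelling site, with one list of label items. The sponsor chooses the route; it should respect the protocol's own 30-day limit.
- State in 7.3 what, if anything, is dispensed at visits beyond collecting and weighing returns, and limit any month-6 dispensing to patients in open-label continuation. Deleting visit dispensing outright could leave that phase without a described supply.
- Print on each label a use-by date derived from the decanting date and the protocol's own 30 days.
- State the fill volume, and that 0.25 ml is the amount per facial half if that is meant, so that the run-out statement and the weighing check agree with the dosing volume.

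If monthly decanting and posting is the arrangement actually in place, the cost is protocol and label wording. If the pharmacy route of 7.2 is in place, some logistics may have to change as well.

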## 7.4 Withdrawal of individual subjects

Subjects can withdraw from the study at any time for any reason if they wish to do so without any consequences. The investigator can decide to withdraw a subject from the study for urgent medical reasons.

## 7.5 Replacement of individual subjects after withdrawal

To have enough power we need at least 17 patients. When the number of patients drops below 17, we will replace them by new subjects.

## 7.6 Follow-up of subjects withdrawn from treatment

When subjects are withdrawn from treatment they come for a follow-up visit after 3 months. Then follow-up will conduct according to regular care.

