## 4.4 Sample size calculation

Sample size is calculated to detect a difference of 35% in response as measured with a 7-point scale with a power of 90% and a type 1 error, 2 sided, of 0.05. Using McNemar’s chi-square test for matched pairs (each patient serves as his/her own control) we would need 17 patients. Taking into account 15% drop-outs we need to include 20 patients.

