## 5.2 Use of co-intervention

The use of topical immunosuppressants in the face, including tacrolimus and corticosteroids and the use of any other facial dermatological medication that is interacting rapamycin, is not allowed. Topical medication that is used outside the face can be allowed after consultation with the principal investigator. Oral immunosuppressive medication is not allowed. Any other oral medication is only allowed after consulting the principal investigator.

Females should ensure adequate contraception using oral contraceptives and barrier methods. Local surgical procedures including laser surgery are not allowed. If there is a medical necessity for such procedures the patient must discontinue the trial.

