# *7.* METHODS

## 7.1 Study parameters/endpoints

### 7.1.1 Main study parameter/endpoint

The main study parameter is the change in lesion size and count (severity) as measured by the investigator, the patient and two independent dermatologists. For lesion size we use the average size of fibrofolliculomas in millimetres.

Severity is indicated on a 7-point scale:

-3= strong worsening

-2= moderate worsening

-1= minimal worsening

0= no improvement

1= minimal improvement

2= moderate improvement

3= strong improvement

Significant regression is defined as a difference in assessment by at least 2 of 3 observers, with at least +2 points. The observers are the investigator and two independent physicians. Assessment of size and count is made on the basis of medical photos of the face. These photos will be standardized; same distance, background, colour and light profile etc.

Confirmation by visual examination.

Professor [name], professor in clinical epidemiology of Maastricht UMC has advised us to use this 7-point scale. Given the fact that there are no previous randomized controlled trials in the BHD syndrome, there is no previously validated scale that we can use for this disease. That is why we have chosen for a 7-point Likert scale. It is known that the Likert scale has good measurement properties and it is used often in trials in which skin changes have to be assessed [19, 20].

During the study we will determine the intra- and inter-observer variability by means of a weighted kappa test. Per patient 2 photographs will be assessed with the 7-point scale; at 3 months and at 6 months. These photographs will be compared with a baseline photo. To measure the inter- and intra observer variability we need at least 3 observers. These observers will be the researcher and two independent physicians. They will assess every photo twice. To prevent bias, the assessments must be at least 2 months apart. Besides evaluation based on photographs, the researcher as well as the patient can assess facial progress during the appointments. These assessments are not included in the analysis, only the results based on the photographs provided by the researcher, physician 1 and physician 2 will be used. This means there will be 6 scores for every patient per follow-up visit. Of these results, the most frequently given score will be used for the analysis.

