## 8.2 Adverse and serious adverse events

Adverse events are defined as any undesirable experience occurring to a subject during a clinical trial, whether or not considered related to the investigational drug. All adverse events reported spontaneously by the subject or observed by the investiga­tor or his staff will be recorded.

When there is a possible adverse event, the trial physician will consult the PI who will then take appropriate action based on his assessment. An example of an adverse event related to the investigational drug (an adverse reaction) is local irritation after application of rapamycin. If this is not allergic, the trial will continue and the patient will get a corticosteroid temporarily. When local irritation is based on an allergic reaction the patient will be excluded.

When a local side effect appears, the affected side of the face will be recorded on the study forms so that it is possible to check afterwards whether the adverse event was caused by rapamycin or the placebo.

A serious adverse event is any untoward medical occurrence or effect that at any dose results in death;

- is life threatening (at the time of the event);
- requires hospitalisation or prolongation of existing inpatients’ hospitalisation;
- results in persistent or significant disability or incapacity;
- is a congenital anomaly or birth defect;
- is a new event of the trial likely to affect the safety of the subjects, such as an unexpected outcome of an adverse reaction, lack of efficacy of an IMP used for the treatment of a life threatening disease, major safety finding from a newly completed animal study, etc.

All SAEs will be reported to the accredited METC that approved the protocol, according to the requirements of that METC.

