## 9.2 Primary analysis

During the trial patients apply rapamycin solution in one facial half and placebo solution in the other facial half. This means that the patient is his/her own control.

Primary output measure is change in facial fibrofolliculoma size and count (severity) as measured by the investigator, two independent physicians and the patient. The response to treatment will be assessed with a 7-point rating scale, ranging from -3 (strong worsening) to +3 (strong improvement). This scale is described in chapter 7. Significant regression is defined as assessment by at least 2 of 3 observers with at least +2 points. Rapamycin will be compared with placebo using a McNemar ‘s chi square test for paired samples. Both an intention to treat and a per protocol analysis will be performed.

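### Section 7.6 does not keep patients who stop treatment on the 3- and 6-month photographs that the promised intention-to-treat analysis needs

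*Protocol*

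**What the plan says.** Section 7.1.1 fixes when the outcome is measured: "Per patient 2 photographs will be assessed with the 7-point scale; at 3 months and at 6 months". Each photograph is compared with the baseline photograph. Only the photograph scores of the three observers enter the analysis; assessments made in person at the visits do not.

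Section 9.2 then states: "Both an intention to treat and a per protocol analysis will be performed".

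For patients who come off treatment, section 7.6 says: "When subjects are withdrawn from treatment they come for a follow-up visit after 3 months. Then follow-up will conduct according to regular care". It gives no starting point for the 3 months and mentions no photograph.

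Two other sections deal with particular reasons for stopping. On irritation, section 8.2 says: "When local irritation is based on an allergic reaction the patient will be excluded". On surgical and laser procedures, section 5.2 says: "If there is a medical necessity for such procedures the patient must discontinue the trial". Neither says whether outcome photographs continue afterwards.

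Section 4.4 needs 17 patients and enrols 20 to allow for 15% drop-out. Section 7.5 replaces patients if the number falls below 17. Section 3 ends the trial for an individual patient whose lesions worsen, or who shows no improvement after 3 months. Section 7.3 describes medical photography as part of regular care.

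**The concern.** An intention-to-treat analysis needs the outcome of every randomized patient at the planned times, whether or not the patient is still on treatment. No section of the protocol keeps patients who stop treatment on the month-3 and month-6 photographs. Section 7.6 gives them a single visit of uncertain timing and then releases them from the trial's schedule.

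Whether a photograph is taken is a matter of data collection. A statistical analysis plan can say how to handle a missing score, but it cannot supply a photograph that was never taken. Replacement under section 7.5 restores the number of patients, not the outcome of the one who left.

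Some exits may be related to the result. Allergy is a tolerability exit, and worsening is itself an outcome. Losses of that kind cannot be assumed to be random.

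**Working it through.** **1. The plan's own figures.** Inputs from section 4.4: "type 1 error, 2 sided, of 0.05", 90% power, and a sample size "to detect a difference of 35% in response as measured with a 7-point scale", tested by McNemar. The split of discordant pairs is not given. Assume 35% of patients respond on the rapamycin side only and 0% on the placebo side only, so that total discordance s and difference d are both 0.35. Miettinen's formula gives

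n = [1.960·s + 1.282·√(s² − d²(3+s)/4)]² / (s·d²) = (0.686 + 0.181)² / 0.0429 ≈ 17.5,

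close to the stated 17. Drop-out: 17 / (1 − 0.15) = 20.0, so the planned loss is 0.15 × 20 = 3 patients. The finding does not depend on how 17 was obtained, only on the 3.

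**2. Visit calendar under both readings of section 7.6.** Counted from stopping, the visit falls at stop month + 3. Counted from baseline, it falls at month 3.

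| Stop at month | Visit, from stopping | Month-3 photo | Month-6 photo | Month-3 photo, from baseline | Month-6 photo, from baseline |
|---|---|---|---|---|---|
| 1 | 4 | not secured | not secured | visit occurs, photo not required | not secured |
| 2 | 5 | not secured | not secured | visit occurs, photo not required | not secured |
| 3 | 6 | already taken | visit occurs, photo not required | already taken | not secured |
| 4 | 7 | already taken | not secured | already taken | not secured |
| 5 | 8 | already taken | not secured | already taken | not secured |

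Of these cases, only a stop at month 3 with the months counted from stopping brings the patient back at month 6, and even then no photograph is required.

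**3. How much three pairs can matter.** This is an assumed illustration; the protocol contains no such data. With 17 pairs and a 35% difference, 0.35 × 17 ≈ 6 discordant pairs favour rapamycin. The uncorrected McNemar statistic is (b − c)²/(b + c).

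- 6 vs 0: 36/6 = 6.0, p = 0.014 (exact 0.031).
- One missing patient is a placebo-side-only responder, 6 vs 1: 25/7 = 3.57, p = 0.059 (exact 0.125).
- All three are, 6 vs 3: 9/9 = 1.0, p = 0.317 (exact 0.508).
- One missing patient is a rapamycin-side-only responder, 7 vs 0: 49/7 = 7.0, p = 0.008 (exact 0.016).
- The missing patients responded on neither side or on both: the pairs are concordant and nothing changes.

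**4. What retention could give.** With 35% vs 0% discordance the statistic equals b, so b ≥ 4 is significant. Power is P(Bin(n, 0.35) ≥ 4), which is 89.7% at n = 17 and 95.6% at n = 20. If 5% respond on the placebo side only and the difference stays at 35%, power is 62.8% and 70.4%; with 10%, it is 49.9% and 57.3%. The figures for 20 assume the same effect in patients who stopped, so they are an upper limit on the benefit.

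**The case against.** The strongest reply is that the gap is narrower than it looks, and much of that reply stands.

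- A reader might infer that the intention-to-treat analysis has no outcome for anyone who stops. The text does not support this. A patient who stops at or after month 3 should already have that photograph, and section 3 aims to keep patients on treatment for at least 3 months. For the no-effect stop at month 3, a visit 3 months later falls on month 6.
- A reader might take section 7.6 to mean 3 months after stopping. It does not say so. The defect is that the origin is open, and month 6 is unsecured for most stoppers on either reading.
- Section 7.6 does not rule out a photograph, and section 7.3 counts photography as regular care. Images may exist, but on no trial schedule. The outcome is unsecured rather than known to be absent.
- A reader might infer that the intention-to-treat set collapses into the per-protocol set. That presumes a complete-case rule which the protocol does not state and an analysis plan may settle.
- Not every exit is related to treatment. Under section 8.2 non-allergic irritation does not end participation, and procedures or personal reasons need not be linked to the drug. Sections 7.4 and 7.6 also treat leaving the study and stopping treatment separately.
- In a split-face design a lost patient removes both sides at once, so the arms cannot lose different patients. The loss can still depend on the difference between the sides.
- The 6 vs 0 pattern is a chosen example. A patient who stopped early may well have responded on neither side, which leaves the test unchanged.

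None of this supplies a rule that photographs be taken at months 3 and 6 after treatment has stopped.

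**Conclusion.** The point holds in limited form. As written, section 7.6 does not secure the month-6 photograph for most patients who stop, and for those who stop before month 3 it may secure neither. By the protocol's own allowance this concerns up to 3 of 20 patients.

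The direction and size of any effect on the result cannot be predicted: depending on the missing pairs it may be nil, favourable or unfavourable. The p-values above show only that a comparison of about 17 pairs is sensitive to a few patients.

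The conclusion rests on the absence of any section that keeps stoppers on the photograph schedule. It also depends on which visit carries the primary comparison, which sections 7.1.1 and 9.2 do not name. If month 3 does, only stops before month 3 matter; if month 6 does, almost all do. It is a weakness worth correcting because the correction is cheap, not one that invalidates the design.

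**What to change.** In section 7.6, state that patients who stop study medication without withdrawing consent keep the month-3 and month-6 visits counted from baseline. Each visit should include the standardized photograph, read by the same blinded procedure and included in the intention-to-treat analysis. This also removes the doubt about the time origin.

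Reconcile the wording on exclusion in section 8.2 and on leaving the trial in section 5.2 with section 7.6, so that it is clear whether outcome follow-up continues. This need not change any rule on when treatment stops. Record any facial procedure that precedes a photograph, since the image may then reflect the procedure; how such images are used can be left to the analysis plan.

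The cost is wording in three sections and one or two extra visits for early stoppers, with photography that section 7.3 already counts as regular care. Enrolment stays at 20. The downside is that some patients may decline, so the gap will shrink rather than close.
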